## Work stream 2: Primary studies on the tailoring process

Primary research will be carried out to investigate the role of stakeholders, evidence and theory within the prioritisation and selection stage of tailoring, informed by the findings of the evidence synthesis workstream. This research will involve individual studies to tailor strategies to support the implementation of EBI in the Irish health system, to answer questions about the tailoring process and its core components. Our first study is currently underway. The design of specific studies and the tailoring question they aim to address will be informed by the results of the scoping review.

### Study 1: Tailoring strategies to support the implementation of Dose Adjustment for Normal Eating (DAFNE), a group patient education programme for adults with type 1 diabetes

**
*DAFNE*
**

We are conducting a mixed methods study to develop tailored strategies to support the implementation of the structured diabetes education programme for people with type 1 diabetes, Dose Adjustment for Normal Easting (DAFNE) (
Box 1). DAFNE is the only structured education programme that is currently available in Ireland that meets all the criteria of the clinical recommendations regarding structured patient education and thus, has been prioritised for roll-out as part of National Clinical Guideline (Adult type 1 diabetes mellitus) in Ireland
^
39
^. It is a UK-led programme involving several Irish centres. To become a DAFNE centre, at least one Diabetes Nurse and one Dietitian must train as DAFNE educators, and one physician must train as a DAFNE doctor. Evaluations of DAFNE, both in the UK and Ireland, have focused on effectiveness and psychosocial outcomes
^
47–
50
^ but little is known about how the programme is implemented across sites and how best to support implementation. Previous studies identified challenges with the implementation of structured diabetes education programmes, including delivery of specific elements of the programme
^
51
^, and patient non-attendance
^
52–
54
^.

Box 1. Overview of Dose Adjustment for Normal Easting (DAFNE)5-day training course for people with type 1 diabetesGroups of 6–8 participants are given guidance by two certified educators (one diabetes specialist nurse and one diabetes dietitian), allowing participants to learn by experience and practice the key skills of estimating carbohydrate and adjusting insulin dose. A two to three hour group follow-up session is offered to participants at 4–12 weeks after each course to consolidate the skills acquired during the course and to review targets and goals.In response to COVID-19, some centres offered remote DAFNE, which is a blend of online learning, workbook activities and remote group sessions facilitated by DAFNE educators.Since COVID-19, more DAFNE Central administrators have started offering the DAFNE ‘buddy’ system which involves a call twice a year to offer support, for example, with entering data, training etc. Any issues are fed back to either clinical educators / trainers or operational staff. DAFNE training and delivery has also moved online.

There are potentially 20 DAFNE sites eligible for this study at different phases of implementation
^
55
^. At the time of writing, eleven DAFNE centres are already established in Ireland (sustainment). Two centres started delivering courses in 2022 (early implementation), and seven have expressed an interest in or are in the process of joining the DAFNE consortium and expect to be established in 2022 (preparation). As the centres are at different stages of implementation, we have an opportunity to explore tailoring both as a process to identify anticipated determinants and select new tailored strategies to support implementation (early sites), and potentially modify existing strategies to improve and sustain a programme (at established sites). We also have an opportunity to examine readiness for implementation at newer sites, evaluating this before and after the tailoring process.

### Objectives

Our specific objectives for this study are:

1. To examine patterns of programme implementation across DAFNE sites (UK and Ireland)2. To understand determinants (barriers and enablers) of implementation in Ireland

3. To work with DAFNE educators in Ireland to develop tailored implementation strategies to support the implementation of DAFNE and further our understanding of decision-making during the prioritisation and selection stage, specifically:▪How do stakeholders make decisions about what to prioritise and what to select?▪What additional guidance and evidence do they use and value during the prioritisation and selection?

4. To evaluate the feasibility and outcomes of the tailoring process (to understand how best to support this practice in the health system).

### Design and methods

We are conducting a mixed methods study of a structured group consensus-based process. All Irish centres will be invited to take part in three group sessions to work through the steps of the tailoring process: 1. determinant identification, 2. determinant prioritization and 3. selection of strategies, varying the guidance and evidence provided at each step (
Figure 2). Where appropriate, the selected strategies will be applied and evaluated in a future study.

**Figure 2. f2:**
[figure not shown]
Overview of DAFNE tailoring sessions.

### Recruitment

**
*Health professionals*
**

Participants invited to take part in the tailoring process include professionals who are currently involved in or due to be involved in the delivery of DAFNE at each centre (dieticians, diabetes nurse specialists, consultant physicians, and administrators). We anticipate a minimum of three participants to be included at each site.

Centres are being invited to take part in the study via email or phone by hospital site lead clinical investigators and co-investigators from the National Clinical Programme for Diabetes. Teams are provided with an overview of the study and advised that they are under no obligation to take part.

**
*Service users*
**

Service users may be invited to participate in a session to discuss and operationalise strategies if patient-level strategies are proposed by centres. Service users will include those who have already attended a DAFNE course or are eligible (and have been invited) to attend the programme. Service users will be adults aged 18 or over, with type 1 diabetes, representing a mix of ages, and genders. Multiple discussion sessions will be held as centres progress through the tailoring process and as strategies are proposed. Service users will have the option to take part in more than one discussion session if they wish. It is anticipated 4–5 service users will be invited to take part in each discussion session.

Service users will be invited via HCPs delivering the DAFNE programme. People who are signed up to attend DAFNE or have recently attended the programme will have the option to contact researchers who will then follow up with them to confirm their interest. Service users will be purposively sampled from respondents who contact the research team. If it is not possible to recruit service users through DAFNE centres, other recruitment avenues will be used: social media posts, Diabetes Ireland clinics and support groups, and information distributed at local and community events. 

All professionals and service users are invited to read a participant information sheet and provide explicit consent to participate in the study.

To date, eight centres are actively participating in the tailoring process. Ethical approval has been granted for six further centres. Ethical approval for five other centres is pending.

### Data collection

**
*Quantitative data on implementation*
**

To understand delivery of the DAFNE programmes at different DAFNE centres in the UK and Ireland, we are accessing and analysing (1) anonymised service-level data and participant-level data held by the Central DAFNE Coordinating Centre (1
^st^ January 2019 – 1
^st^ January 2021)
*and* (2) service-level data held by local centres [one-year pre-COVID-19 (2019) and the most recent years of the programme (2020, 2021, 2022)].

**Central DAFNE data**

Irish centres submit data on course delivery and participants on an annual basis. Where feasible, these data are being used to identify aspects of implementation that may need to be improved. The following anonymized data from Central DAFNE is being accessed to understand the profile of participants and programme delivery:

- Year of birth, sex, ethnicity, year dx, height, weight, HbA1c, number of severe hypoglycaemia episodes and diabetic ketoacidosis (DKAs) of programme participants pre and post course attendance.- Number of DAFNE courses delivered, number of attendees, dropouts / course completion (number of days completed), reasons for dropouts, curriculum delivered.

**Local data**

The following anonymized data from local sites is being accessed, where feasible, to understand the profile of participants and programme delivery: Number of people eligible, number of people invited, and number who accepted course.

### Tailoring process

Each step involves a 1-hour group discussion session, conducted online or face-to-face depending on what is most feasible for participants. Sessions are being facilitated by FR, a postdoctoral researcher with a PhD in Health Services Research, and experience of conducting qualitative research with health care professionals and patients. FR does not have a prior relationship with participants. Professionals involved in DAFNE delivery and service users (who have been invited to or attended DAFNE) attend separate sessions. The sessions were piloted with a group of doctoral students who are also clinicians and known to the study authors.

**
*Session 1: Determinant (barrier and enabler) identification and initial prioritisation*
**

Prior to the first session, participants are asked to complete a survey to describe the characteristics of their DAFNE site. This survey includes validated scales
^
56,
57
^ to assess inner setting measures as per the Consolidated Framework for Implementation Research (CFIR) (culture, implementation climate, learning climate, leadership engagement, available resources) and readiness for implementation
^
58
^. Newly established centres at the early stages of implementation will be asked about their readiness for implementation. Data are analysed to understand their unique contexts (e.g., resources, staffing, experience with implementation) and the factors that potentially influence the tailoring process and its feasibility in the health service. As part of this survey, to streamline determinant identification
^
59
^, they are asked to consider a list of determinants, indicate whether each determinant is a barrier or enabler at their site, and to supplement or remove determinants from this list as they relate to their experience of implementation. This list is based on rapid evidence review of the existing literature on the implementation of structured diabetes education programmes. 

During the first session, discussions are semi-structured and guided by a topic guide to further consider determinants at their site. Participants are asked to initially prioritise their top ten determinants based on their own assumptions individually using an interactive ranking tool, called Slido
^
60
^. They are asked to discuss their reasons for prioritisation.

**
*Session 2: Final determinant prioritisation with guidance and evidence*
**

During the second session, participants are asked to consider the prioritised determinants taking into account specific criteria: the feasibility of addressing a determinant, importance, and chronicity [how frequently the determinant arises in practice or persists over time]. Where available, the research team present additional evidence about ubiquity [how pervasive a determinant is, operationalised as the extent to which a determinant comes up in the international literature and across other Irish centres], and criticality [how likely is the determinant to affect the implementation outcome, operationalised as whether other studies cite the determinant as influential]. Lastly, participants are asked to initially brainstorm what strategies might address the determinants they have prioritised. By exploring the use of additional criteria (chronicity, ubiquity, criticality) we are building on research conducted by the Optimising Implementation in Cancer Control (OPTICC) centre in the US, which proposed these criteria as a way to overcome the limitations of typical criteria used to prioritise determinants (feasibility and importance) which are not clearly linked to impact
^
61
^.

**
*Session 3: Strategy selection*
**

During the final session, when selecting strategies, participants are asked to consider evidence of effectiveness and alignment with prioritized determinants based on existing guidance. Participants are presented first, with strategies they proposed in Session 2 mapped to determinants. If there are strategies which were not mapped to specific determinant(s), participants are prompted to explain how they expect the strategy would work and what it would target.

Second, they are presented with prioritised factors mapped to the Expert Recommendations for Implementing Change (ERIC) strategies
^
7
^ highlighting the % agreement based on expert consensus
^
62
^ and acknowledging the limitations of this matching. Participants are asked to select strategies from this list and discuss the reasons for their selection. If available, participants are presented with (systematic review) evidence corresponding to the strategies they have selected. If evidence of strategy effectiveness is unavailable, they are prompted to indicate whether additional evidence (and what type of evidence) would influence their decisions. Lastly, they are asked to select two strategies to focus on and these are further operationalised in the session, prompting them to specify Actor, Action Target, Temporarily, Dose, Outcome and Justification
^
63
^. If patient-level strategies are selected, in a separate session service users are asked to provide feedback on these strategies and what they should look like (how they should be operationalised) from their perspective.

### Data analysis

**
*Quantitative analysis*
**

Anonymised data obtained from DAFNE Central will be analysed using Stata. Descriptive statistics will be generated (mean (sd), median (range), frequencies, percentages) to understand the demographic and clinical profile of people attending DAFNE, compare DAFNE participant profiles pre and post course attendance, and understand course delivery across centres. Variables such as centre and country will be examined as predictors of course completion using logistic regression.

Survey data will be inputted (if paper-based) or downloaded (if online) to Excel for quality checks and cleaning before being imported into Stata for analysis. Survey data will be analysed descriptively (frequencies and percentages). For measures of the inner setting (culture, learning climate, available resources, leadership engagement), mean scores will be calculated across respondents at each site. For the organisational readiness measure, mean scores will be calculated at a subscale level (change commitment and change efficacy) and at the overall readiness level (i.e., combined change commitment and change efficacy).

**
*Qualitative analysis*
**

Qualitative analysis will be conducted with the support of NVivo software for data management. Transcripts will be coded using the Framework Method
^
64
^, which is a form of thematic analysis. This approach is suitable for projects with prespecified objectives such as evaluating acceptability and feasibility. It also allows unexpected themes to emerge during initial phases of familiarisation and open coding.

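### The course-completion regression names centre and country as predictors without handling the nesting; read as single-level, it gives either no country estimate or one that is too precise

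*Protocol article*

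**What the plan says.** Study 1's first objective is "To examine patterns of programme implementation across DAFNE sites (UK and Ireland"), and Table 1 gives course completion as one example of such a pattern. The Data collection section describes the source as "anonymised service-level data and participant-level data held by the Central DAFNE Coordinating Centre", covering 1 January 2019 to 1 January 2021. The outcome is among the items listed under Central DAFNE data: "dropouts / course completion (number of days completed), reasons for dropouts, curriculum delivered".

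The Quantitative analysis paragraph is mostly descriptive: "Descriptive statistics will be generated (mean (sd), median (range), frequencies, percentages"). It then adds one model: "Variables such as centre and country will be examined as predictors of course completion using logistic regression". The software is Stata. The text does not say whether the two variables enter together or separately, whether centre is fixed or random, or how clustering is treated.

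On structure, Box 1 says that courses are taught to six to eight people by two educators. The Study 1 description says that "eleven DAFNE centres are already established in Ireland (sustainment") and "Two centres started delivering courses in 2022 (early implementation"). The latter two began after the central data window closed, so at most about 11 Irish centres can contribute. The number of UK centres is not given.

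**The concern.** Centre and country are named side by side as if they were interchangeable predictors, but one determines the other. Country varies only between centres, while the data are at participant level. A single-level model therefore treats each participant as an independent observation about country, when the independent units are the centres.

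This is the only regression in Study 1's quantitative analysis. The article says that the central data will be used, where feasible, to find aspects of implementation needing improvement. A UK–Ireland difference that looks more certain than it is could direct attention to the wrong problem. A coefficient labelled country that in fact compares two arbitrary reference centres could do the same.

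**Working it through.** The article states no sample size, significance level, ICC or completion rate for this analysis, so there is no figure to reproduce. Three checks follow. From the article come the 11 established Irish centres, the two countries and the course size of 6 to 8. All other inputs are assumptions.

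**1. Both variables as fixed factors.** With an intercept, a country indicator and indicators for all centres but one, the country column is an exact linear combination of the others.

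- 11 Irish + 20 UK centres: 32 columns, rank 31.
- 11 Irish + 70 UK centres: 82 columns, rank 81.

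The shortfall is exactly one whatever the number of UK centres. Software will omit a column and may still print a country coefficient, but that number then depends on which centres serve as reference. This check needs no assumption about the data.

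**2. Country without centre.** For equal centre sizes n and ICC ρ, the design effect is DE = 1 + (n − 1)ρ. The true standard error is √DE times the naive one. A nominal two-sided 5% test rejects with probability 2[1 − Φ(1.96/√DE)] when there is no country effect.

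| n per centre | ρ | DE | true SE / naive SE | actual rejection rate |
|---|---|---|---|---|
| 14 (2 courses of 7) | 0.01 | 1 + 13 × 0.01 = 1.13 | 1.06 | 6.5% |
| 14 | 0.05 | 1.65 | 1.28 | 12.7% |
| 14 | 0.10 | 2.30 | 1.52 | 19.6% |
| 56 (8 courses of 7) | 0.01 | 1.55 | 1.24 | 11.5% |
| 56 | 0.05 | 3.75 | 1.94 | 31.1% |
| 56 | 0.10 | 1 + 55 × 0.10 = 6.50 | 2.55 | 44.2% |

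Clustering by course alone matters less. With 6 to 8 per course, DE is 1.05 to 1.07 at ρ = 0.01 and 1.50 to 1.70 at ρ = 0.10. Centre is the level that must be handled.

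**3. Would cluster-robust standard errors be enough?** A simulation used 11 Irish and (assumed) 60 UK centres, 4, 8 or 16 courses of 7 per centre, 90% completion, ICC 0.02 to 0.10 and no country effect, with 400 runs for each of nine settings. The ICC here is on the latent logistic scale, so these results do not line up cell by cell with the table.

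- Naive standard errors: rejection from 6% to 40%.
- Centre-clustered standard errors: rejection from about 5% to 12%. The nine settings average 0.72/9 = 8.0%.
- Clustered standard errors averaged 1.04 to 2.11 times the naive ones.

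Clustering removes most of the excess but not all of it, because one arm of the comparison has only 11 clusters. In a separate simulation (11 Irish and 40 UK centres, 6 courses of 7, 90% completion), a centre-level t-test rejected about 6% of the time. The mixed model itself was not simulated.

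**The case against.** The strongest reply is that the sentence is short and permissive. It does not call the model ordinary, does not put both variables in one model and does not exclude random effects. A model with country fixed and centre random is also logistic regression and fits the wording. The article condenses a five-year programme, and such detail may sit in a fuller plan. The analysis describes patterns, and no hypothesis, significance level or decision rule attaches to the country coefficient.

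Much of this stands. A reader might infer that the plan definitely fits an unidentifiable model, or that the country effect will be far too precise. The documents support neither: the first is one reading, and the size of the second depends on assumed ICCs and centre sizes.

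Two further inferences also go too far.

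- **Centres with no dropouts would be lost from a fixed-centre model.** With 5% dropout, 0.95^14 = 49% or 0.95^42 = 12% of centres would have none. With 90% completion and 42 per centre, it is 0.90^42 = about 1%. The article gives no dropout rate.
- **The country contrast is confounded with delivery format.** Box 1 does say "In response to COVID-19, some centres offered remote DAFNE". But an illustrative unadjusted odds ratio of 0.71 (0.86 against 0.896 completion) rests wholly on invented completion rates and remote shares. Remote delivery may also be part of the implementation pattern that the objective wants to describe.

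What the reply does not remove is that the article names a method and two nested predictors. On the plain reading of that method, the country result is either missing or over-precise.

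**Conclusion.** The point holds in a limited form. The nesting is a fact of the design. Non-estimability under joint fixed effects is exact and needs no assumption. If country is fitted alone, the direction of the error is certain whenever completion varies between centres. Its size is not: the standard-error ratio is about 1.06 to 2.55 for assumed ICCs of 0.01 to 0.10 and 14 to 56 participants per centre of equal size. Smaller between-centre variation would make it negligible, and larger centres would make it worse.

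It should be fixed before the analysis is run. It is not critical, because the regression is exploratory within a largely descriptive section and no formal test is stated.

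**What to change.** Replace the sentence with a mixed-effects logistic regression of course completion: country as a fixed effect, a random intercept for centre, and a random intercept for course within centre where course identifiers are available. Report centre differences as the between-centre variance with shrunken centre estimates, not as a list of centre coefficients. Do not rely on cluster-robust standard errors alone with 11 Irish centres; use the mixed model or a centre-level comparison.

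Adjustment for delivery format, calendar period and case-mix can be added as a sensitivity analysis. It is optional, because it answers a different question from the overall pattern.

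The cost is a change of wording and a request for centre and, if held, course identifiers in the extract. The country confidence interval will be wider, which reflects the information actually available.
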